**4.0 Research Design**

The proposed research design includes the utilization of randomized controlled trial methods in order to evaluate integrated health and housing services. The project involves two sub-populations of homeless individuals, characterized by different eligibility criteria: one group with “high needs” and a second group with “moderate needs”. The project thus consists of two related but distinct RCTs which differ with regard to the severity of participants’ needs, the number of intervention arms, and the type of intervention services. Despite these differences, many of the major methodological features of each RCT will be the same. These include: participant recruitment and retention strategies, tests and measures of outcomes of interest, study hypotheses, and plans for data analysis. In addition, both RCTs incorporate qualitative and quantitative methods along with the secondary analysis of administrative data.

Participants with high needs will be randomized to one of two *Housing First* program variations (Scattered-site + ACT or Congregate + ACT\*) or to a Treatment as Usual (TAU) group (see Figure 2). Participant choice will be maximized in all study conditions, and all study participants who are randomized to an intervention group will receive some form of low-barrier housing as well as intensive support services. Moderate need participants will be randomized to one of two groups, an intervention (Scattered-site + ICM) or TAU group. Please see Section 4.4 for details on the housing and support interventions as well as the TAU group.

[figure not shown]

\*Intensive treatment services will be integrated into the congregate housing condition. In the event that an ACT team cannot be developed in this condition, the service component will consist of a comparable range and intensity of services.

All study participants will be followed and re-interviewed every 6 months for a period of 2 years from baseline. A field office will be established to facilitate tracking and interviewing of participants. The field office will be utilized as a confidential location for conducting follow-up interviews as well as a place where participants can ask questions about the project, their next interview (e.g., date, time, etc.), and update their contact information.

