2. **Full Screening:** If pre-screening criteria are satisfied, participants will be asked the full set of screening questions. This will include evaluation of full inclusion and exclusion criteria, including classification as high or moderate need. Classification as *high*-need will correspond to Section 3 of Ontario Standards for ACT, as set forth by the MHCC. Classification as *moderate*-need will also be based on the same criteria; however, participants will be excluded if their score on the Symptom Checklist-90-R exceeds a threshold (to be determined) appropriate for the ICM condition. The

proportion of potential participants who fall into the high vs. moderate needs groups will be tested empirically during the implementation phase of the project.

Screening will be computer-based and will inform the interviewer whether or not the participant meets the study inclusion criteria as well as their level of need. Participants will be asked to return to the field office the following day to complete the **baseline evaluation** and then to receive notification of group assignment. In order to facilitate follow-up, participants will be asked to provide locations/ services they frequent regularly. This requirement to return the following day may pose a barrier to recruitment and recruiters will be trained to actively seek people who do not return.

**Randomization** will be performed separately for the two need groups (high and moderate). To control for initial differences among groups, randomization strata will include with or without substance use problems and absolute homelessness or precariously housed. Randomization will be performed using a block technique with variable block size using prepared tables. When participants return the next day to complete the baseline evaluation, they will receive notification of group assignment in a sealed envelope along with an information package; at this time, a field office worker will accompany participants who are assigned to an active intervention to the service provider's location. Those randomized to TAU will be informed about available services in the community. All participants will be invited to use the field office as a resource centre.

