##### 4.6.2.1 Surveys and Questionnaires

The survey instruments consist of previously validated measures recommended by the National Project Team. We have also proposed a number of additional relevant measures. Copies of instruments are presented in Addendum B. Please see Appendix 5.0 for a summary of the timing of administration.

Housing status over the preceding 6 months will be determined at baseline and at the time of each follow-up interview using the Housing Timeline Follow-Back Calendar (HTFBC). The primary outcome variable will be housing status at the time of the 2 year follow-up interview, defined as being either: (1) Homeless, or (2) Stable Housing (living for a continuous period of at least 90 days in a house,

 The SOS is based on the core of the modified Overt Aggression Scale (see Addendum for a copy of this instrument).

apartment, SRO hotel, rooming house, or any other place of one's own for which one pays rent; Ontario MCFS, 2004). Other outcome variables to be derived from the HTFBC will include: (1) housing status at each follow-up period; (2) number of housing transitions over the previous 6 months; (3) number of nights spent homeless over the previous 6 months. The Housing Quality Score will be used to determine self-reported quality of current living conditions in terms of comfort, safety, spaciousness, privacy, friendliness and overall quality.

Demographic characteristics will be collected using subsections of the Community Mental Health Evaluation Initiative (CMEI). Quality of life will be assessed using two instruments: (1) The Quality of Life for Homeless & Hard to House Individuals (QOLHHI) Instrument (Hubley & Palepu, in preparation); and (2) the EuroQol (EQ5D), a standardized health-related quality of life instrument that generates a composite score reflecting the preference value associated with a given health state, and a global rating of current health using a visual analog scale. General functioning will be assessed using the Multnomah Community Ability Scale (MCAS). Resiliency will be assessed using the 3-item Sense of Coherence Scale. Vocational outcomes will be assessed using a timeline follow-back interview from the Montreal IPS study (indicated by MHCC), which examines work status and various details of work (e.g., setting, timing, hours, compensation, etc.).

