**Quantitative Data Analysis**

In its most basic form, each RCT can be viewed as a mixed-effects 2 by 5 model (or in the case of the high needs group, a 3 by 5 model) with a number of different outcome measures of interest based on specific hypotheses (see section 2.3 for the outcome measures) and a number of potential covariates. The hypotheses address comparisons of specific sub-groups within the overall model.

The general analysis plan proposes several broad strategies of data analysis that will build upon the data as it is collected over the study period. The approach to analysis will begin with a baseline examination of the distribution of key factors across each sub-group. This univariate comparison of the distributions of key individual characteristics (e.g., demographic characteristics, substance abuse and mental health indicators) across each RCT sub-group will provide for an assessment of the effectiveness of the randomization process as well as identification of potential confounding factors that need to be accounted for in further analyses. Preliminary steps for all analyses will also involve assessing bivariate cross-tabulations and correlation matrices for relationships among variables. All variables will be checked with regard to their distribution (e.g., for normality and departures from normality) using frequency distributions, scatter plots and histograms. Statistics such as means, standard deviations, ranges, modes, medians and estimates of skewness and kurtosis will be computed.

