We propose to assess our primary and secondary hypotheses using two approaches. The first (and simplest) is to perform cross-sectional analyses at each of the five measurement points (baseline, 6 months, etc.) comparing the 5 distinct intervention groups on the measure of interest at each point in time. Depending on the measure, this can be done using a non-parametric comparison for the categorical measures such as physical health status or parametric comparison (with confidence intervals) for the continuous measures (such as number of days housed). Plotted over time, this approach can provide a straight-forward and visual assessment of the relationship between the various interventions and the outcomes of interest. This approach, however, does not take into account the role of time or the variation within-groups over time specified in the hypotheses. Thus, we propose to conduct a number of longitudinal repeated measures analyses with the choice of the exact model depending on the intent of the individual hypotheses. We will begin with Generalized

Estimating Equations (GEE), adding in the specific interaction terms of interest as specified in the various hypotheses. This approach is based on specific assumptions around the pattern of missing data and will be adjusted as need be. An alternative approach is in the assessment of individual trajectories and draws from random effects models. Random effects models allow for a measure of variability in individual trajectories around the average group trajectory and are especially useful when it is reasonable to think of individual trajectories as a sample from the population of homelessness trajectories. All models will be implemented utilizing software applications which have the capability of modeling complex error structures at both the across individual (e.g., each person has their own trajectory of homelessness) as well as the within-individual (e.g., auto-correlated error structures of individuals' responses within their across time homelessness trajectory) levels.

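### The first approach to the hypotheses compares all five groups at every wave, baseline included, and is not confined to comparisons within each separately randomised trial

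*Protocol*

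**What the plan says.** Protocol section 4.9 (Quantitative Data Analysis) introduces its methods with "We propose to assess our primary and secondary hypotheses using two approaches". The first approach is to "perform cross-sectional analyses at each of the five measurement points (baseline, 6 months, etc", and its content is "comparing the 5 distinct intervention groups on the measure of interest at each point in time". Categorical measures get a non-parametric comparison and continuous measures a parametric one with confidence intervals. The results, plotted over time, are meant to show how the interventions relate to outcome. The only weakness that the section admits is that time and within-group change are ignored. For that reason it goes on to GEE and random-effects models.

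Other parts of the protocol describe a different structure:

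- Section 4.0: "The project thus consists of two related but distinct RCTs". The high-need trial has three arms (scattered-site + ACT, congregate, TAU) and the moderate-need trial has two (scattered-site + ICM, TAU).
- Section 4.3: randomisation "will be performed separately for the two need groups (high and moderate" needs).
- Section 4.9, shortly before the sentence at issue: "each RCT can be viewed as a mixed-effects 2 by 5 model", or a 3 by 5 model for the high-need trial.
- Section 4.6.2.1: "The primary outcome variable will be housing status at the time of the 2 year follow-up interview". Housing status at each follow-up is listed among the other outcome variables.

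**The concern.** Only arms of the same trial were randomised against each other. A comparison of, say, the ICM arm with high-need TAU mixes the intervention with need level, and need level is fixed by eligibility. The wording does not limit the comparison to a trial and mentions no stratification or adjustment for need.

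The problem is sharpest for the second primary hypothesis, mental health. Section 4.3 removes moderate-need candidates who score above an SCL-90-R threshold, and section 4.6.1 proposes the SCL-90 for symptoms. The eligibility rule therefore separates the two populations on the scale, or its close relative, on which the hypothesis would be judged.

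Listing baseline among the waves at which hypotheses are assessed adds a smaller fault. No intervention effect can exist at that point, and section 4.9 already provides a separate baseline description to check the randomisation.

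**Working it through.** The protocol gives no alpha, power or effect size, so there is no figure of its own to reproduce.

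**Group size.** Section 4.6.1 samples 20 per group as 20% of participants, 100 in all. So 20 / 0.20 = 100 per group, and 5 × 100 = 500, which agrees with section 5.1.

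**Contrasts.** Five groups give 5 × 4 / 2 = 10 pairs. Within trials there are 3 (high need) + 1 (moderate need) = 4. Across trials there are 3 × 2 = 6, none of them randomised. The primary hypotheses in section 4.1 set Housing First against TAU. That needs three of the four within-trial pairs and none of the six others.

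**Five-group test on a continuous score.** Assumptions: no intervention effect in either trial, a two-sided 5% level, and a need-level gap of d SD. With three group means at 0 and two at −d, the grand mean is −0.4d and the sum of squared deviations is 3 × 0.16d² + 2 × 0.36d² = 1.2d². The noncentrality is 100 × 1.2d² = 120d², with 4 and 495 degrees of freedom.

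| Assumed gap d (SD) | Noncentrality | Probability of rejection |
|---|---|---|
| 0 | 0 | 0.05 |
| 0.1 | 1.2 | 0.12 |
| 0.2 | 4.8 | 0.38 |
| 0.3 | 10.8 | 0.75 |
| 0.5 | 30 | 0.997 |

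A simulation of 4,000 runs gave 0.75 at 0.3 SD and 0.997 at 0.5 SD.

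**One cross-trial pair.** At 0.3 SD, z = 0.3 / √(2/100) = 2.12, and the probability of exceeding 1.96 is 0.56.

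**Stable housing.** Here the documents support no particular gap. As an illustration only, 30% in all high-need arms and 40% in both moderate-need arms gives a mean of 0.34, a noncentrality of 100 × 1.2 × 0.10² / (0.34 × 0.66) = 5.35 on 4 degrees of freedom, and a rejection probability of 0.42.

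**Unstratified pooling of Housing First against TAU.** High-need participants would be 200/300 of Housing First and 100/200 of TAU. The bias is d × (2/3 − 1/2) = d/6, or 0.05 SD when d = 0.3.

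**Within-trial comparison.** In the same simulation, a three-arm test inside the high-need trial rejected in 5.3% to 5.4% of runs at gaps of 0, 0.3 and 0.5 SD. The need-level gap no longer matters.

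**The case against.** The strongest reply is that no pooled test is specified. The sentence names the groups but gives no omnibus statistic, no alpha and no cross-need contrast. Sections 4.0 and 4.3 and the per-RCT framing in 4.9 all point to within-trial comparisons, and 4.9 adds that the hypotheses concern particular sub-groups. The protocol also presents this step as the simplest, largely visual one, and then moves to longitudinal models. A rejection across five groups would not in any case establish Housing First over TAU.

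Much of this stands. The omnibus test, the 5% level and the gaps are assumptions of this review, and the threshold on the SCL-90-R is still open. What does not fall away is that the step is declared a way to assess the primary hypotheses, and that nothing in its wording applies the within-trial restriction.

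A reader might infer three stronger points, which the documents do not support:

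- *That every planned analysis is confounded by need level.* The GEE and random-effects models can be fitted per RCT, and the 2 by 5 and 3 by 5 framing suggests that they would be.
- *That testing at several waves inflates the error rate of the primary result.* Section 4.6.2.1 fixes housing at two years and places earlier housing status among other outcomes. Rules for multiplicity and testing order are commonly left to a statistical analysis plan, which was not available here.
- *That moderate-need participants will certainly have better housing outcomes.* The SCL-90-R cut supports a symptom gap at entry but says nothing about housing at 24 months.

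**Conclusion.** The point holds as a conflict within section 4.9, and between it and sections 4.0, 4.3 and 4.6.2.1. As written, the first approach admits six non-randomised contrasts out of ten and would let need level appear as an intervention difference. If it were carried out as a five-group test, the false rejection rate would run from 5% with no gap to about 12%, 38% and 75% at gaps of 0.1, 0.2 and 0.3 SD. These figures rest on 100 per group, no intervention effect, a 5% level and assumed gaps. The direction does not depend on them, because any true gap raises the rate above 5%. For an unstratified pooled Housing First against TAU contrast the harm is much smaller, one sixth of the gap. The defect is confined to the first approach.

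**What to change.** In section 4.9, replace the five-group comparison with wording to this effect: all comparisons are made within each RCT, namely scattered-site + ACT against high-need TAU, congregate against high-need TAU, and scattered-site + ICM against moderate-need TAU; any combined Housing First against TAU estimate is stratified by need level; baseline values are described and not used to assess hypotheses; for housing, the 24-month comparison is primary and the 6-, 12- and 18-month comparisons are supportive. Plots may still show all five groups if they are set out by trial.

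The cost is a change of wording. It needs no further participants, visits or data, and it gives up no comparison that the randomisation supports.

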#### **4.5 Follow-up and Retention Procedures**

Careful tracking will be critical to ensure a high response rate and to minimize attrition bias, particularly for the TAU group. Steps to retain participants will include regular contacts with all participants at 6-month intervals over the course of the 2 year follow-up and regularly updating contact information gathered from administrative data, participating service providers and public records. The TAU group will be encouraged to visit the field office on a monthly basis to check in with staff and to update their contact information. In addition to the remuneration they receive for participating in the five interviews, participants in this group will receive a \$10 honorarium for each month that they check in. Food will also be available to further encourage field office visits. For those participants who cannot be located in-person or reached by phone, outreach workers in the community will inquire about their whereabouts. Locating these participants will require the full-time efforts of trained field workers (e.g., peer researchers) who are well-embedded in the community and are familiar with following homeless individuals over a period of time.

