#### **4.6.3 Cost Outcome Analyses & Administrative Data**

All study participants will be asked to provide consent for the research team to utilize their personal identifiers (i.e., name, date of birth, personal health number) to obtain administrative data reflecting their health care utilization (hospital, physician services, prescriptions), social services utilization (income assistance, disability and unemployment benefits) and criminal justice encounters (arrests and Provincial sentences). The research team at CARMHA has extensive experience collaborating with government agencies in the linkage and analysis of these data. The costs associated with service events have been established through previous studies by CARMHA and the Provincial Government, and will be the basis for econometric analyses in the current study.

Data will be sought retrospectively to 1996, enriching our understanding of the trajectories of service utilization preceding study participation. These data will be refreshed and updated each year through

the active study period (2009-2013), and then bi-annually until 2019. Funds to support research following the study period will be sought separately.

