#### **4.9 General Approach to Data Analysis**

##### **Quantitative Data Structure**

The data structure for the quantitative analyses is outlined in Table 2 below (which presents the general structure of this data file for a single participant [case 01] who is assumed to have been interviewed in each of the five waves of data collection). The first row (shaded) shows the structure of the baseline study used for cross-sectional analyses. The five rows taken together represent the repeated data over the course of the study period. All analyses will be based on an intent to treat.

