**Definitions:**

**X** = A vector of variables and/or indicators representing individual characteristics whose values do not change over time. Examples include gender, age at entry, race/ethnicity and group intervention.

**$Y_i$**  = A vector of variables and indicators whose values at baseline may need to be repeatedly updated. Examples are psycho-social indicators such as family structure, income, indicators of social capital (family, marital status and social network indicators), human capital (schooling and employment status), indicators of resiliency (sense of coherence) and other events (e.g., a serious illness or injury) that occurred in the 6 months prior to the  $i^{th}$  interview.

**$Z_i$**  = A vector of indicators of alcohol, drug and mental health status as of the  $i^{th}$  interview. The time frame for these measures extends from “past week” or “last 30 days” to “last 6 months”.

**$H_i$**  = A vector of indicators of housing circumstances in the 6 months prior to the  $i^{th}$  year interview. See the discussion of these measures under Aim 1 below.

**$S_i$**  = A vector of indicators of services used during the 6 months prior to the  $i^{th}$  interview. These include services connected to receipt of the interventions (e.g., substance abuse treatment or work programs). These data will consist of information from records as well as self-reports.

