**Analytic Limitations:** *Missing Data.* A concern throughout the analyses is the effect of missing data due to item non-response as well as panel attrition. In the case of missing data due to item non-response among persons who participate in a cycle of data collection, we plan to implement imputation methods, particularly for critical variables utilized in the cross-sectional presentation of the results. In general, we will use multiple imputation methods (Rubin, 1987) involving MCMC simulations. Available methods (Rubin, 1987) will be used to combine analysis results from multiple imputations that incorporate the uncertainty due to item non-response in the estimates of parameter variances. Models based on GEE (or related) approaches do not require the estimation of missing data.

*Panel attrition.* This is often more influential than item non-response on the comparison of groups. We will begin with a comprehensive investigation of baseline characteristics associated with patterns of participation will be examined by study follow-up wave to help identify the characteristics associated with trends in participation over time. Variables found to be significantly associated with attrition will be included as covariates in the models.

*Power considerations.* In light of the well-defined criteria established by the MHCC surrounding the sample size of each intervention arm as well as the understanding that the MHCC criteria takes account of panel attrition, no power calculations were conducted within the context of this application.

*Administrative Data.* The administrative data will be linked and incorporated with the quantitative data based on the appropriate vector of variables (see Table 2 above). Quantitative data analyses will be conducted drawing from these data in the same manner as that of data collected in the study.

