### 5.3 Administrative Data.

**Risk to Subjects:** *Human Subject Involvement.* All study participants will be asked to provide consent for the researchers to utilize their personal identifiers (i.e., name, date of birth, personal health number) to obtain administrative data reflecting their health care utilization (hospital, physician services, prescriptions), social services utilization (income assistance, disability and unemployment benefits) and criminal justice encounters (arrests and Provincial sentences). Data will be sought retrospectively to 1996 and will be refreshed and updated each year through the active study period (2009-2013), and then bi-annually until 2019.

**Potential risks.** This study component involves minimal potential risks to participants. However, a potential risk associated with collection of the administrative data surrounds embarrassment and discomfort in the event that the individual's identity is compromised. In order to minimize this potential risk, the electronic dataset used for the analyses proposed here will include *no personal identifying information*. Results will be reported in ways that do not reveal respondent identities.

**Adequacy of protection against risks.** *Informed consent.* During the consent procedures we will emphasize that: a) participation is completely voluntary; b) even after consenting to participate, they may refuse access to their administrative data; c) and no personal identifying information will appear in any materials associated with the study. No identifying personal information about the study participants will be kept with any of the administrative data. Records linking participant's study identification number and administrative data will be kept under lock by the Project Manager at CARMHA. All personal identifiers will be removed from the administrative data as soon as possible.

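### Service use taken from administrative records is tied to the six months before each interview, so read literally it is undefined at a missed wave and gapped or overlapping at a late one

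*Protocol*

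**What the plan says.** Three parts of Section 4.9 bear on this.

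- **Definitions under Table 2.** The service vector S is "A vector of indicators of services used during the 6 months prior to the" i-th interview. The same definition adds: "These data will consist of information from records as well as self-reports". The interview window is therefore written for record data too.
- **Administrative Data paragraph.** "The administrative data will be linked and incorporated with the quantitative data based on the appropriate vector of variables (see Table 2 above"). The next sentence reads: "Quantitative data analyses will be conducted drawing from these data in the same manner as that of data collected in the study".
- **Quantitative Data Structure.** The file layout is shown for one participant "who is assumed to have been interviewed in each of the five waves of data collection". No layout is given for a missed wave.

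On missing data, Section 4.9 confines multiple imputation to item non-response among people who took part in that wave. It notes that GEE does not need missing values to be estimated, and it handles attrition by adding associated variables as covariates.

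The records follow a different clock. Sections 4.6.3 and 5.3 seek them back to 1996. Section 4.6.3 adds that "These data will be refreshed and updated each year through" the active study period (2009 to 2013), and then bi-annually to 2019. Neither section makes collection depend on an interview. On follow-up, Section 4.5 calls for careful tracking to "minimize attrition bias, particularly for the TAU group".

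**The concern.** Interview attrition is unavoidable for self-reported outcomes, because nobody recorded the missing time. It is avoidable for hospital, physician, prescription, income assistance, arrest and sentence records, which accrue whether or not the participant is found for interview. If the analysis window exists only where an interview exists, outcomes that need not suffer attrition acquire it.

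The outcomes at stake are secondary hypotheses 2 (costs and component services), 6 (justice involvement) and the income assistance part of 7. If waves are missed more often in one arm, and service use while out of contact differs from use while in contact, the comparison between arms is distorted. That also sits poorly with the intent-to-treat commitment in Section 4.9, since data on randomised participants would be left out because an interview failed.

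**Working it through.** The plan states no figure to reproduce on this point: no attrition rate, event rate, alpha or power calculation. The check is therefore a reading of the definitions, followed by arithmetic on labelled assumptions.

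**1. Where the window comes from.** In the Section 4.9 definitions, the only vector not tied to an interview is X, which holds characteristics that do not change. Y, Z, H and S are all defined relative to the i-th interview. S names records as a source. Costs and justice events are not named in any vector. Section 4.6.3 bases costs on service events and counts justice encounters among the administrative data, and the Administrative Data paragraph sends such data to a Table 2 vector. Whichever time-varying vector is chosen, the written anchor is the interview.

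**2. A missed wave.** With no i-th interview, the six months before it have no defined start or end. Imputation does not apply, because it covers attended waves only. GEE uses the rows that exist. The share of 24-month follow-up affected is 6/24 = 25% per missed wave.

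**3. A late wave.** Suppose the 12-month interview is held at month 15, with the others on time. Its window is months 9 to 15, so months 6 to 9 fall in no window: 3/24 = 12.5% of follow-up. The 18-month window is months 12 to 18, so months 12 to 15 are counted twice.

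**4. Volume.** Section 5.1 gives 500 participants and four follow-up interviews: 500 × 4 = 2,000 windows, or 12,000 person-months. Assuming everyone consents to linkage and a share *q* of waves is missed:

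| *q* (assumed) | windows without a value | person-months | SE inflation at a wave, 1/√(1−*q*) |
|---|---|---|---|
| 10% | 200 | 1,200 | 1.05 |
| 20% | 400 | 2,400 | 1.12 |
| 30% | 600 | 3,600 | 1.20 |

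With windows fixed from randomisation, a missed interview would cost none of these.

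**5. Possible bias.** Let *p* be the share of waves held and *m* the event rate in unseen time relative to seen time, with *m* the same in both arms. The observed mean is 1/(*p* + (1−*p*)*m*) of the true mean. The observed Housing First to TAU ratio is the true ratio multiplied by [*p*_T + (1−*p*_T)*m*] / [*p*_H + (1−*p*_H)*m*]. For a true ratio of 1.00:

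| *p*_T / *p*_H (assumed) | *m* = 0.5 | *m* = 1 | *m* = 1.5 | *m* = 2 |
|---|---|---|---|---|
| 0.90 / 0.90 | 1.00 | 1.00 | 1.00 | 1.00 |
| 0.75 / 0.90 | 0.875/0.95 = 0.92 | 1.00 | 1.125/1.05 = 1.07 | 1.25/1.10 = 1.14 |
| 0.70 / 0.90 | 0.85/0.95 = 0.89 | 1.00 | 1.15/1.05 = 1.10 | 1.30/1.10 = 1.18 |

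In the middle row with *m* = 2, the TAU mean is 1 − 1/1.25 = 20% too low and the Housing First mean is 1 − 1/1.10 = 9% too low. A true ratio of 1.10/1.25 = 0.88 would then read as 1.00. Bias needs both unequal retention and *m* different from 1. Its sign depends on which arm loses more waves and on whether *m* is above or below 1.

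**The case against.** The strongest reply is that the protocol nowhere says records are dropped. Table 2 labels its rows by nominal time (baseline, 6 months and so on), so record windows could be tied to scheduled dates. The instruction to analyse records like the other data may mean only that the same models are used. The records also plainly have a life outside the interview windows: they go back to 1996, continue to 2019, and have their own linked database and retrospective analysis in the Section 9.0 workplan. Section 4.6.3 does not tie costing to interviews. Interval boundaries and merge rules commonly belong in a statistical analysis plan, and that document is not at hand.

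Much of this stands. A reader might infer that the plan throws away complete records at every missed wave. The text does not support that: it says neither that they are dropped nor that they are kept. Coverage is not complete either, since Section 5.3 lets participants refuse access and justice data are limited to arrests and Provincial sentences. A reader might also infer that the plan forecasts the worst attrition in TAU. Section 4.5 only names TAU as the group of particular concern, and sets monthly check-ins with a $10 honorarium against the risk. The plan also allows covariates for attrition and adjustment of the GEE approach to the missing-data pattern.

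What the reply does not remove is the definition of S. It states an interview window and states that records fall within it. That is a rule already written into the protocol, not a detail left open for later, and an analyst following it would meet the problem at the first missed wave. Covariate adjustment is also a weak substitute for using outcome data that can be obtained.

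**Conclusion.** The point holds as a defect of definition affecting secondary outcomes, and it should be corrected. Read literally, Section 4.9 leaves record-based service use undefined at missed waves and gapped or overlapping at late ones, despite linked records for participants who consented. Costs and justice events are affected only if they are placed in the same structure, which the protocol does not expressly say.

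The firm quantities are structural: 25% of follow-up per missed wave, and 12.5% uncovered for a wave three months late. Everything on bias is illustrative, because retention and event-rate multiples are assumptions. It would be tempting to conclude that the plan understates TAU service use and so biases the comparison against Housing First. The documents do not support this: people who cannot be found may use services more, or may have moved away or died and use them less, and no rates are given. The supportable conclusion is avoidable and possibly differential missingness in secondary hypotheses 2, 6 and the income assistance part of 7.

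**What to change.** In the Section 4.9 definition of S and in the Administrative Data paragraph, state that:

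- outcomes taken from administrative records are counted in fixed intervals from the date of randomisation (0–6, 6–12, 12–18 and 18–24 months);
- they are counted for every randomised participant with linkage consent, whether or not the interview was held;
- the days covered by the records in each interval are the exposure, which allows for withdrawn access, death and incomplete coverage;
- costs and justice events derived from records follow the same rule;
- the interview-anchored window is kept for self-reported services only.

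The cost is some wording and a different merge key. No new data, interviews or participants are needed. The one drawback is that self-reported and record-based windows will differ slightly for the same participant, which should be noted wherever the two sources are compared or combined.
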